#### Common versus specific factors

Do common factors (e.g. therapeutic alliance, therapist competence and adherence to the therapy model) differentially influence outcome in the two treatment modalities?

We will test the following hypothesis:Therapeutic alliance is rated significant higher (WAI) for patients who have improved (lower BDI II scores) in the PDT arm compared to patients who have improved in the CBT arm.No significant differences in the patients score regarding therapist competence and adherence to the therapy model (WAI) will be obtained between the two groups for patients who improves (BDI II).

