Four studies [8, 16, 49, 63] have examined personality traits or disorders as moderators of response to IPT and CBT. Overall, the findings suggest that both borderline PD and an avoidant attachment style predict better response to CBT, while the results of one of the studies suggest that patients with obsessive–compulsive PD may experience better response to IPT [8]. These studies were limited by low number of participants. Other studies have found the presence of PD to predict poorer outcome across treatments when comparing CBT to IPT [44]. Thus, whether a co-occurring PD or a distancing attachment style moderate outcome of CBT versus short-term PDT is not known.

The therapeutic alliance refers to the relationship between the therapist and the patient, and to what extent they agree on treatment goals and therapeutic tasks, and form a positively toned emotional bond 2013,55. The alliance is considered a common factor in psychotherapy (e.g. therapeutic alliance, patient expectancy, therapist competence and adherence to the therapy model), and has been shown through meta-analyses to influence outcome equally across different variants of psychotherapy [42]. These meta-analyses have, however, examined the influence of alliance on a group level rather than as a moderator of treatment in subgroups of patients. Few previous studies have explored how alliance may moderate outcomes across various treatments, and even fewer studies have focused on interactions with patient characteristics as possible moderators [59]. Consequently, we still do not know whether alliance is more important in certain therapies, or for certain patients [6].

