#### Self-report

An extensive battery of self-report questionnaires is used; The Working Alliance Inventory (WAI-SR_1) [43] assess alliance, the Experience in Close Relationships (ECR) [20] evaluates attachment style and Inventory of interpersonal problems (IIP-64) [2] taps interpersonal distress. The Structural Analysis of Social Behaviour (SASB) [37] also assess interpersonal and intrapsychic interactions, and Severity Indices of Personality Problems-Short Form (SIPP-SF) [82] is used to assess personality problems.

Questionnaires that assess childhood trauma, Childhood Trauma Questionnaire (CTQ) [17], work and social adjustment, WSAS [65], emotional awareness/alexithymia, the Toronto Alexithymia scale (TAS-20) [4] will also be used at several time points during therapy and at follow up.

Metacognitions are assessed using Meta Cognitive Questionnaire (MCQ-30) [85], cognitive insight using Becks Cognitive Insight Scale (BCIS) (Aaron T. [13], dysfunctional attitudes using the Dysfuntional attitude scale (DAS) [14] Rumination related scales are used, including the Positive Beliefs about Rumination Scale (PBRS) [69] Negative Beliefs about Rumination Scale (NBRS) and Ruminative Response Scale (RRS) [78].

Depressive symptoms are assessed using Becks Depression Inventory (BDI) [15] and manic/hypomanic symptoms using Hypomania Checklist-32 [3]. Levels of anxiety are assessed using GAD-7 [74]. In addition sociodemographic are recorded and health related quality of life is assessed by Short-Form 12 (SF-12) [84].

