## Intervention: CBT compared to PDT for treatment of patients with MDE

### Therapists

The psychotherapy with CBT and PDT are conducted by therapists from Nydalen and Vinderen psychiatric outpatient clinic, who have completed a minimum of two-year training in CBT and PDT. In addition, all therapists receive specific training in the CBT and PDT study manuals prior to commencing as therapists in the study. All treatment sessions are videotaped and independent psychiatrists will carry out assessment of treatment fidelity on a selection of random tapes.

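### The common-factor hypotheses compare WAI between arms among improvers only, which cannot separate a higher mean alliance from a different alliance-outcome relation; hypothesis 2 also uses WAI for competence and adherence and counts non-significance as support

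*Protocol article*

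**What the plan says.** The section *Common versus specific factors* in the protocol article asks whether common factors such as alliance, competence and adherence "differentially influence outcome in the two treatment modalities". It then sets two hypotheses to be tested.

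- Hypothesis 1: "Therapeutic alliance is rated significant higher (WAI) for patients who have improved (lower BDI II scores) in the PDT arm". The comparator is the improvers of the other arm.
- Hypothesis 2: "No significant differences in the patients score regarding therapist competence and adherence to the therapy model (WAI) will be obtained". This too sets the arms against each other among those who improve on BDI II.

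Elsewhere the article says what WAI measures and how fidelity will be assessed.

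- *Self-report* section: "The Working Alliance Inventory (WAI-SR_1) [43] assess alliance".
- *What works for whom? (Moderators)*: alliance is the patient-therapist relationship and "to what extent they agree on treatment goals and therapeutic tasks, and form a positively toned emotional bond". The same paragraph lists the common factors as "therapeutic alliance, patient expectancy, therapist competence and adherence to the therapy model", so competence and adherence stand beside alliance, not inside it.
- *Therapists* section: all sessions are videotaped and "independent psychiatrists will carry out assessment of treatment fidelity on a selection of random tapes".
- Table 1 lists therapist adherence as its own entry next to WAI.

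The *Statistical analysis plan* section says that moderation by variables other than the mediator is estimated with an interaction term in the regression. It does not link this to the common-factor hypotheses.

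**The concern.** The question is about a relation: does a given difference in alliance go with a larger difference in outcome in one arm than in the other? The hypotheses are about a level: is mean WAI higher in PDT improvers than in CBT improvers? There are three difficulties.

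1. Improvement is a post-randomisation result. Restricting to improvers gives up the randomised comparison and removes the patients needed to see how alliance varies with outcome within an arm.
2. If PDT patients simply rate the alliance higher, hypothesis 1 is confirmed with no differential influence. If alliance matters more in PDT but is rated lower there, a real differential influence can be hidden.
3. Hypothesis 2 counts a non-significant result as support for similarity, and the instrument it names does not measure competence or adherence by the protocol's own description.

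This is one of the three stated research areas, and these are its only two hypotheses.

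**Working it through.** **The protocol's own power figure.** The *Power analysis* section gives 26 / 64 per group for d = 0.8 / 0.5 (80% power, 5% level). A two-sided two-sample t-test gives 25.5 and 63.8, which round up to 26 and 64. The figure reproduces. It concerns the total effect; the article gives none for the common-factor hypotheses.

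**Assumptions for the check (none is in the protocol).** 50 patients per arm (100 in total is stated). WAI and outcome each have SD 1 and are normal. Mean outcome and improver share are equal in the arms. The improver share is 50% (0.50 × 50 = 25 per arm) or 84% (0.84 × 50 = 42 per arm). The stated contrast is taken as a two-sided t-test at 5%; the article names no test.

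**What the contrast estimates.** Let Δ be the PDT-minus-CBT difference in mean WAI, and b_P and b_C the alliance-outcome slopes in SD per SD. Among improvers the expected WAI difference is

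Δ + k·(b_P − b_C), with k = φ(z) / share,

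where z is the cut-off for improvement and φ the normal density.

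- Share 50%: k = 0.399 / 0.50 = 0.80.
- Share 84%: k = 0.243 / 0.84 = 0.29.

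Δ and the slope difference enter as one sum, so the contrast cannot tell them apart. The weight on the slope difference, which is the quantity of interest, shrinks as more patients improve.

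**Rejection rates.** Simulated at 50 per arm, at least 4,000 trials per scenario. The two middle columns count trials in which PDT is significantly higher among improvers. The last column is the arm × WAI term in all 100 patients.

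| Scenario | Improvers, 25/arm | Improvers, 42/arm | Interaction |
|---|---|---|---|
| No influence in either arm, Δ = 0.5 | 40% | 62% | 5% |
| No influence in either arm, Δ = 0.8 | 79% | 95% | 5% |
| Equal influence (0.3 in both), Δ = 0.5 | 43% | 64% | 5% |
| Influence in PDT only (0.5), Δ = 0 | 30% | 10% | 73% |
| Influence in PDT only (0.5), Δ = −0.40 | 3% | under 1% | 73% |

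The first three rows have no differential influence, so every confirmation there is false. In the first two rows the contrast is an ordinary t-test of a true gap, so the rate is simply its power (exact: 41% and 62% at 0.5 SD). In the last row with 25 per arm, −0.40 + 0.80 × 0.5 = 0, so the real difference in influence cancels.

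**Hypothesis 2.** Power of the t-test at a true difference of 0.5 SD, and the resulting chance of non-significance:

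- 25 per arm: power 41%, non-significant in 59% of trials.
- 42 per arm: power 62%, non-significant in 38%.
- All 50 per arm: power 70%, non-significant in 30%.

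The protocol's own figure of 64 per group for a medium effect exceeds even the full arm.

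**Limits of the interaction.** At a slope difference of 0.3 with N = 100, its power is only about 31–34%.

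**The case against.** The strongest reply has five parts.

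- **The section states hypotheses, not an analysis.** It names no test, WAI time point or cut-off for improvement, and the *Statistical analysis plan* section already describes interaction terms. This stands in part: the recommended method is in the document. But it is not tied to these hypotheses, and the population, the variable and the predicted result are explicit in them.
- **The figures rest on assumptions.** This stands. Lower BDI II scores could, read literally, cover most patients, so a reader might infer a halved sample that the documents do not state. A larger share of improvers makes hypothesis 2 less weak but raises false confirmation of hypothesis 1. With no WAI gap and no influence, the stated contrast confirms in only about 2.5% of trials.
- **The contrast is not blind to a slope difference.** This stands. A reader might infer that it can show nothing, or that it must give a wrong answer in both directions. The documents do not support that: it reacts to a slope difference (30% and 10% in the fourth scenario) but cannot attribute its result to one.
- **Attaching WAI to competence and adherence may be a labelling slip.** Possible, since Table 1 lists therapist adherence separately. The passages still need reconciling.
- **WAI is itself measured after randomisation.** True. The interaction is therefore not a purely randomised comparison either, and the fix must say so.

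**Conclusion.** The point holds in this form: the two hypotheses do not isolate the quantity the section asks about, and hypothesis 2 names an instrument that the protocol describes as measuring something else. The mismatch follows from the text and needs no numbers. Its size is illustrative. With an assumed 0.5 SD gap in mean WAI and no influence on outcome, hypothesis 1 is confirmed in about 40% of trials with 25 improvers per arm and 62% with 42, against 5% for the interaction. A true 0.5 SD difference under hypothesis 2 is non-significant in 59% and 38% of trials.

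A reader might infer that the trial's main aims are compromised. They are not: *Aims* centres the planned analysis on moderators and mediators, and correcting this changes neither the design, the primary outcome nor those analyses. It should be fixed, but it is not a fatal fault.

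**What to change.** **Hypothesis 1.** Restate it as the arm × WAI term in a regression of later BDI-II (for example week 28) on arm, early WAI, their interaction and baseline BDI-II, in all randomised patients. Week-8 WAI can also be adjusted for week-8 BDI. Week-3 WAI cannot be adjusted for concurrent symptoms, because patients complete only WAI then.

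**Hypothesis 2.** Replace WAI with the planned therapist-adherence measure, the tape-fidelity ratings, or both. Test the arm × fidelity term on outcome in the same way; comparing mean fidelity between arms would again leave outcome out. Report estimates with 95% confidence intervals and drop the absence of a significant difference as the criterion.

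**Interpretation.** State that WAI and fidelity arise after randomisation, so the interaction is an association adjusted for measured confounders. State also that power is limited for modest slope differences.

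**Cost.** Two hypotheses are reworded and regressions are run on data already planned. Fidelity ratings cover only sampled tapes, so that analysis will have fewer patients. Table 1 as it reads here shows therapist adherence only in the baseline row, so the timing of that measure should be confirmed first.

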### Aims

Primary outcome of the study will be depressive symptoms assessed with both Hamilton Depression Rating Scale (HDRS) and Beck Depression Inventory II (BDI II). As we expect PDT and CBT to be equally effective, the overall aim of the MOP study is to examine mechanisms of change in psychotherapy and examine specific markers of psychotherapy outcome (moderators). Consequently, the planned analysis refers to the putative moderators and mediators. The study will focus on research questions within the following areas:

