**Fig. 2 Fig2:**
[figure not shown]
Causal diagram for mediation, A: treatment, M: mediator, Y: outcome and C: measured confounders

Randomization of treatment group also strengthens assessment of effect heterogeneity/moderation, from other variables than the mediator. This is estimated by including an interaction term in the regression.

Direct and indirect effects are generalizable to time-varying mediators, but with similar assumptions as mentioned above. Without time-varying confounders for the mediator—depression relationship that are affected by the group-assignment, the natural direct/indirect effects are identifiable (in addition to the controlled direct effect) in longitudinal equivalents. With a time-varying confounder affected by group-assignment, only the longitudinal equivalent of the controlled direct effect is identifiable, and can be estimated with the marginal structural model [81]. Also, a time-varying moderator effect is identifiable in a structural nested mean model, and can be estimated by g-estimation (Vansteelandt 2016).

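### Alliance hypothesis compares WAI only among improvers, so it cannot show whether alliance influences outcome differently in PDT and CBT

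*Protocol article*

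**What the plan says.** The subsection Common versus specific factors (under Aims) poses the question: "Do common factors (e.g. therapeutic alliance, therapist competence and adherence to the therapy model) differentially influence outcome in the two treatment modalities". The background section on moderators describes the gap in the same terms: "we still do not know whether alliance is more important in certain therapies, or for certain patients". Both concern how strongly alliance acts on outcome in each arm.

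The hypothesis that the protocol says it will test is a different one: "Therapeutic alliance is rated significant higher (WAI) for patients who have improved (lower BDI II scores) in the PDT arm". The comparison group is the CBT improvers. The second hypothesis, on therapist competence and adherence, has the same restriction. It predicts that no significant difference "will be obtained between the two groups for patients who improves (BDI II").

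BDI-II, which defines improvement here, is also half of the primary outcome: "depressive symptoms assessed with both Hamilton Depression Rating Scale (HDRS) and Beck Depression Inventory II (BDI II").

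The Statistical analysis plan section does name a method for moderation, in the text after Fig. 2: "This is estimated by including an interaction term in the regression". It is given for moderators in general and is not tied to the alliance hypothesis.

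**The concern.** The question asks for outcome given alliance, compared between arms. The hypothesis gives alliance given a good outcome, compared between arms. Four problems follow.

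- **No alliance-outcome relation can be estimated.** With non-improvers left out of both arms, the association cannot be estimated in either arm, so neither can its difference.
- **Randomisation no longer protects the contrast.** Improvement is known only after treatment, and improvers in PDT and CBT may be different kinds of patient.
- **A level difference passes for an effect.** If PDT patients in general rate the alliance higher, the hypothesis is supported even when alliance does nothing.
- **The definition of improved is loose.** It is given only as lower BDI-II scores. If nearly everyone scores lower, the test becomes a simple arm comparison of WAI.

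A positive result would be reported as alliance mattering more in PDT, and a real difference in influence could go unseen. This is one of the three research areas listed under Aims.

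**Working it through.** **The plan's own figure.** The Power analysis section gives 26 and 64 per group for effect sizes 0.8 and 0.5 (80% power, 5% level). A two-sided two-sample t-test gives 25.5 and 63.8, which round up to 26 and 64. The figure reproduces and is not in dispute.

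**Inputs.** The protocol plans 100 patients, so 50 per arm with equal groups. It gives no WAI means, correlations or improvement rates, so those below are assumptions. WAI has SD 1 in each arm with mean μ. Improvement is a continuous score with SD 1 and correlation ρ with WAI. Improvers are the fraction p above a cut c.

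**What the improver-only contrast measures.** Under bivariate normality the mean WAI among improvers is μ + ρ·λ(p), where λ(p) = φ(c)/p and c = Φ⁻¹(1 − p). The PDT minus CBT contrast is therefore

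Δ = (μ_PDT − μ_CBT) + ρ_PDT·λ(p_PDT) − ρ_CBT·λ(p_CBT).

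The protocol's question concerns only ρ_PDT against ρ_CBT. In Δ that difference is shrunk by λ and mixed with the mean WAI difference and with any difference in improvement rates. The values needed are:

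- λ(0.40) = 0.3863/0.40 = 0.966
- λ(0.50) = 0.3989/0.50 = 0.798
- λ(0.65) = 0.3704/0.65 = 0.570
- λ(0.70) = 0.3477/0.70 = 0.497
- λ(0.80) = 0.2800/0.80 = 0.350

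As p approaches 1, λ approaches 0 and only the mean WAI difference is left.

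**Four cases.**

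1. Alliance has no effect in either arm and WAI is 0.5 SD higher in PDT: Δ = 0.5 + 0 − 0 = 0.5, so the hypothesis looks true.
2. Correlation 0.5 in PDT and 0 in CBT, equal mean WAI: Δ = 0.5 × λ(p) = 0.399, 0.285 and 0.175 with 50%, 65% and 80% improvers.
3. As case 2 with 65% improvers and WAI 0.3 SD lower in PDT: Δ = −0.3 + 0.285 = −0.015, so a real difference in influence vanishes.
4. Correlation 0.3 in both arms, equal mean WAI, but 70% improvers in CBT and 40% in PDT: Δ = 0.3 × (0.966 − 0.497) = 0.141, about 0.14 SD from selection alone.

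**How often each test succeeds.** Simulated trials with 50 per arm (8,000 per scenario for the first three scenarios, about 3,000 for the last two). Success means two-sided p < 0.05 with PDT higher (improver-only t-test on WAI) or with the steeper slope in PDT (arm-by-WAI interaction in all 100, HC3 standard errors). Both succeed in about 2.5% of trials under their own null.

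| Scenario | Improvers | Improver-only test | Interaction test |
|---|---|---|---|
| No alliance effect; WAI +0.5 SD in PDT | 50% / 80% | 41% / 60% | 2–3% |
| Correlation 0.5 vs 0; equal mean WAI | 50% / 65% / 80% | 30% / 21% / 12% | about 70% |
| Correlation 0.5 vs 0; WAI −0.3 SD in PDT | 65% | 2% | 71% |
| Correlation 0.3 vs 0.1; equal mean WAI | 65% | 7% | 16% |
| No alliance effect; WAI +0.2 SD in PDT | 65% | 12% | about 2.5% |

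A separate check used slopes of 0.1 in CBT and 0.5 in PDT with 50% improvers. The improver-only test succeeded in 21% of trials with equal mean WAI and 2% with WAI 0.32 SD lower in PDT, against about 55% for the interaction test. With equal slopes (both 0 or both 0.3) and WAI 0.5 SD higher in PDT, the improver-only test succeeded in 39% to 42%.

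**Loss of patients.** If 40% to 70% improve, 20 to 35 patients per arm remain. A t-test for a 0.5 SD difference then has 34% to 54% power, against 70% with all 50.

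**The case against.** The other side has five points.

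- **A hypothesis sentence is not a full test specification.** It names no test, no threshold for improvement and no WAI time point, and the full analysis plan is not shown. That is so, and the t-test and cut-offs above are one reading. But the protocol says this hypothesis will be tested, and both groups are explicitly improvers. An analysis plan that follows the wording inherits the fault.
- **The right tool is already in the protocol.** The Statistical analysis plan section names an interaction term for moderation and argues for keeping a treatment-by-mediator interaction. Nothing links either to the alliance hypothesis, whose contrast is a different one.
- **The scenarios are favourable.** This stands in part. With correlations 0.3 and 0.1 the interaction test has only 16% power, and a 0.2 SD gap in WAI gives 12% false confirmation, not 41% to 60%. Selection bias proper can also be small: with equal slopes of 0.3, equal improvement rates and a true gap of 0.50 SD, the improver-only difference is 0.51. The ordering of the two tests does not change.
- **The replacement has its own assumptions.** This stands. WAI is itself post-randomisation, so the interaction relies on the protocol's assumption of no unmeasured mediator-outcome confounding. The simulated power is also for a model without BDI-II covariates.
- **The matter is subsidiary.** The randomised comparison, the primary outcome and data collection are unaffected. That limits the damage to this research area but does not make its answer interpretable.

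**Conclusion.** The concern holds. As worded, the hypothesis compares alliance levels in two outcome-selected groups and cannot show whether alliance will "differentially influence outcome in the two treatment modalities". That conclusion follows from the wording alone and needs no numerical assumption.

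The size of the error does rest on assumed WAI differences, correlations and improvement rates, with 50 per arm and no dropout. Within the range examined, false confirmation runs from 12% (WAI gap 0.2 SD) to 60% (gap 0.5 SD, 80% improvers). Detection of a true difference runs from 2% to 30%, where the interaction test reaches 16% to 71%. The second hypothesis shares the defect and also treats a non-significant difference as confirmation. The wording must be changed before these analyses are run.

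**What to change.** Replace the improver-only comparison by a regression in all randomised patients:

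- **Outcome:** BDI-II at a visit after the WAI measurement, with blinded HDRS at week 28 as the other primary scale.
- **Terms:** arm, WAI at week 8 or 16, arm × WAI, baseline BDI-II and BDI-II at the WAI visit. Fix one WAI visit in advance. Weeks 8 and 16 suit because BDI is collected alongside WAI there; at week 3 only WAI is. HDRS is not measured during therapy, so its model also takes BDI-II at the WAI visit.
- **Hypothesis:** a steeper WAI-outcome slope in PDT than in CBT, reported as the slope difference with its confidence interval.
- **Assumption:** say that the interaction needs no unmeasured confounding between alliance and outcome, as the protocol already says for its mediation effects.
- **Second hypothesis:** use the same model form for competence and adherence. If the claim is no difference between arms, judge it by a confidence interval against a stated margin, because a non-significant interaction would not prove it.
- **Description only:** mean WAI among improvers by arm may still be tabulated.

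The cost is rewording two hypotheses and their analysis. Table 1 already schedules WAI after sessions 3, 8 and 16, and BDI at baseline, after sessions 8 and 16, and post treatment. Power for realistic slope differences will be modest, and the report should say so.

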### Trial status

Protocol version 2 (November 2018). The first patient was included February, 2017. The study is ongoing and has recruited 63 patients (February, 2020). The last patients will be assessed three years after end of treatment in December 2023 (Table 1).

**Table 1 Tab1:** Overview: assessments administered at research baseline and each follow-up point throughout the trial

Assessment points	Interviews	Self-report questionnaires	Therapist questionnaires
Baseline (0 weeks)	M.I.N.I., SCID-II, PFS, DSRF, GAF, Hamilton	SF-12, WSAS, CTQ, BDI, SIPP-SF, TAS-20, PBRS/NBRS, SASB, ECR, MCQ-30, RRS, GAD-7, BCIS, DAS, IIP-64, HCL-32	WAI, FWC-58, Therapist adherence
After session 3		WAI	WAI, FWC-58
After session 8		SF-12, WSAS, WAI, BDI, SIPP-SF, TAS-20, PBRS/NBRS, SASB, ECR, MCQ-30, Rumination scale, GAD-7 BCIS, DAS	WAI, FWC-58
After session 16		SF-12, WSAS, WAI, BDI, SIPP-SF, TAS-20, PBRS/NBRS, SASB, ECR, MCQ-30, Rumination scale, GAD-7, BCIS, DAS,	WAI, FWC-58
After 28 weeks/post treatment	M.I.N.I. (depression module only) PFS, DSRF, GAF, Hamilton	SF-12, WSAS, WAI, BDI, SIPP-SF, TAS-20, PBRS/NBRS, SASB, ECR, MCQ-30, Rumination scale, GAD-7, BCIS, DAS, IIP-64, HCL-32	WAI, FWC-58
1 year follow up	M.I.N.I.(depression module only) PFS, DSRF, GAF, Hamilton	SF-12, WSAS, BDI, SIPP-SF, TAS-20, PBRS/NBRS, SASB, ECR, MCQ-30, Rumination scale, GAD-7 BCIS, DAS, IIP-64, HCL-32	
3 year follow up	M.I.N.I. (depression module only), GAF, Hamilton	SF-12, WSAS, BDI, SIPP-SF, TAS-20, PBRS/NBRS, SASB, ECR, MCQ-30, Rumination scale, GAD-7 BCIS, DAS, IIP-64, HCL-32	

WAI-SR_1, Working Alliance Inventory; WSAS, The Work and Social Adjustment Scale; SF-12, The 12-item Short Form Health Survey; CTQ, Childhood Trauma Questionnaire; BDI, Beck Depression Inventory; SIPP-SF, Severity Indices of Personality Problems-Short Form; TAS-20, Toronto Alexithymia Scale; PBRS, Positive Beliefs about Rumination Scale; NBRS, Negative Beliefs about Rumination Scale; SASB, Structural Analysis of Social Behaviour; ECR, Experiences in Close Relationships Inventory; MCQ-30, The Metacognitions Questionnaire 30; RRS, Ruminative Responses Scale; BCIS, Beck Cognitive Insight Scale; GAD-7, Patient Health Questionnaire; DAS, Dysfunctional Attitude Scale; IIP-64, Inventory of interpersonal problems; HCL-32, Hypomania Checklist-32

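### The second common-factor hypothesis names the WAI as its measure of therapist competence and adherence, but by the protocol's own account the WAI measures alliance

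*Protocol article*

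**What the plan says.** The section Common versus specific factors (protocol article, Aims) opens with the question "Do common factors (e.g. therapeutic alliance, therapist competence and adherence to the therapy model) differentially influence outcome in the two treatment modalities". Two hypotheses follow.

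- The first concerns alliance: "Therapeutic alliance is rated significant higher (WAI) for patients who have improved (lower BDI II scores) in the PDT arm", compared with improved patients in the CBT arm.
- The second concerns competence and adherence: "No significant differences in the patients score regarding therapist competence and adherence to the therapy model (WAI) will be obtained between the two groups", and it applies "for patients who improves (BDI II").

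Other sections describe the instrument and the constructs.

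- Self-report (Pre-treatment): "The Working Alliance Inventory (WAI-SR_1) [43] assess alliance".
- What works for whom? (Moderators) defines alliance as the relationship between therapist and patient and "to what extent they agree on treatment goals and therapeutic tasks, and form a positively toned emotional bond". The same paragraph names competence and adherence alongside alliance as examples of common factors.
- Therapists: all sessions are videotaped, and "independent psychiatrists will carry out assessment of treatment fidelity on a selection of random tapes".
- Table 1 (Trial status), therapist questionnaires, baseline row: "WAI, FWC-58, Therapist adherence".

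**The concern.** A hypothesis should be tested on a measure of the thing it is about. Here the construct is therapist competence and adherence, and the measure in brackets is an alliance inventory. The article names an instrument, so this is not a detail left for a fuller document to supply. The instrument it names does not fit the article's own description of what that instrument measures.

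If the analysis follows the text, a WAI result that does not differ between arms would be reported as showing that competence and adherence were similar in CBT and PDT. A result that does differ would be reported as showing that they were not. Neither statement would follow, because patients can agree with their therapist on goals and feel a good bond whether or not the therapist keeps to the manual.

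There is also a conditional problem. Both hypotheses carry the label WAI, both are restricted to BDI II improvers, and both contrast PDT with CBT. If they refer to one and the same score, the first needs a significant difference and the second needs its absence.

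**Working it through.** The article gives no figure for this point. Its only sample-size figures, 26 and 64 per group for effect sizes of 0.8 and 0.5 (Power analysis), refer to a total effect and do not bear on it. For the record, a two-sided 5% t-test with 80% power gives 25.5 and 63.8 per group, which round up to the stated 26 and 64. The check is therefore a comparison of text.

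**Step 1: what the WAI measures.** Self-report says alliance. The background definition of alliance has two parts: agreement on goals and tasks, and an emotional bond. Neither part is competence or adherence. No sentence in the article says that the WAI, or any subscale of it, captures either.

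**Step 2: whether the article treats the constructs as distinct.** It does so twice. The opening question of the section lists alliance, competence and adherence as three examples of common factors, and the background paragraph also lists competence and adherence as items separate from alliance.

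**Step 3: whether other measures exist.** Two sources are planned. One is the independent fidelity rating of randomly selected tapes. The other is the adherence entry in Table 1, which stands next to the WAI as its own item. The second hypothesis refers to neither.

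**Step 4: how the two hypotheses compare.**

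| | First hypothesis | Second hypothesis |
|---|---|---|
| Construct | Alliance | Competence and adherence |
| Instrument named | WAI | WAI |
| Rater | Not stated | Patient |
| Patients | BDI II improvers | BDI II improvers |
| Contrast | PDT against CBT | PDT against CBT |
| Prediction | Significantly higher in PDT | No significant difference |

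The instrument, patients and contrast agree. The rater is open in the first row of predictions, and Table 1 lists the WAI under both the self-report and the therapist questionnaires. No subscale or time point is given for either hypothesis. So the mismatch in steps 1 to 3 follows directly from the text, while the incompatibility in step 4 follows only if score and rater are the same.

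**The case against.** The strongest reply is that the bracketed label is a slip. The two hypotheses name different constructs, and a misplaced instrument name is a simpler explanation than a real intention to measure adherence with an alliance scale. A condensed article also commonly leaves rater, subscale and scoring to the full protocol. Part of this stands: it may well be a slip, and missing scoring detail alone would not be a finding. But the label sits inside a stated hypothesis and specifies the wrong measure, so it needs correcting whatever its origin.

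A reader might infer more: that the two hypotheses predict opposite results for the same score in the same patients. The documents do not support that.

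- The predictions are a difference and no significant difference, not reversed directions.
- That the score is the same is inferred from a shared label. The first hypothesis names no rater, and Table 1 has patient and therapist forms of the WAI. A different rater, item set or time point would remove the conflict.

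Nor should a reader infer that the trial collects nothing on adherence. It plans tape ratings and lists an adherence item; they are simply not linked to this hypothesis.

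Finally, it is fair to object that fidelity ratings are not an exact substitute. The article promises ratings of fidelity and does not say that competence is scored. The hypothesis as worded also concerns a score given by patients. Both objections stand and limit the fix.

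**Conclusion.** The measure is wrongly stated. By the article's own definitions the WAI assesses alliance, and a conclusion about therapist competence and adherence drawn from it would rest on alliance data. This holds whichever WAI rater is meant, and it needs no assumption beyond the article's descriptions of the instrument and the constructs.

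The incompatibility of the two hypotheses is conditional. If score and rater are the same, both cannot be supported among improvers; if they differ, the conflict disappears. The article does not settle which.

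The scope is one of two hypotheses in the third of three research areas. The primary outcome, the moderator and mediator hypotheses, the PAI work and the sample size are untouched. No probability is attached: the article gives neither an improvement rate nor an expected WAI difference, and a power figure from assumed values would not measure this defect. The correction should be made before the common-factor analyses, but it is not a threat to the trial's main aims.

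**What to change.** - Remove the WAI label from the second hypothesis.
- Name the measure of adherence from what is already planned: the independent videotape fidelity ratings, the adherence entry in Table 1, or both. In the table that entry appears only in the baseline row, before any session has been rated, so its timing should be confirmed before it is relied on.
- Claim a result on competence only if the chosen ratings score it. Otherwise drop competence from the hypothesis.
- Keep the WAI for the alliance hypothesis, and state whether the patient or the therapist form is used.

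The cost is more than a wording change. A score given by patients is replaced by observer or therapist ratings, so the hypothesis has to be reworded to say so. If the tape ratings are used, only patients with a rated tape contribute. Adherence to a CBT manual and adherence to a PDT manual may not share a scale, so a raw comparison of arm means should be interpreted with caution.

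Testing whether the relation between fidelity and outcome differs by arm would be closer to the section's opening question. It is a new interaction analysis, however, and would have low power in a tape subsample; the article itself expects its least power for moderators. It is best treated as optional and exploratory.
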